## RESEARCH APPROACH

### B. Research methodology

**Study Location:** The study will be conducted in Hospital Sungai Buloh, Selangor, Malaysia.

**Study Design:** It will be an experimental (randomized Controlled Trial) study design, single-blinded among newly diagnosed HIV positive patients who are eligible to commence ART from December 2013 to August 2014. Following enrollment and allocation to study arm, baseline adherence, clinical symptoms, CD4 count, viral load, Weight, TB status and Opportunistic infection index will be assessed and measured for the 2 groups, prior to the commencement of ART. The intervention group will receive appointment and medication reminders by text-messaging and telephone calls, in addition to standard care. Based on the Theory of Planned Behaviour Model (Ajzen, 1985), appointment reminders will be sent by Short Text Message (in Malay and English languages) three days prior to each individual client's scheduled appointment and telephone call reminders a day prior to the scheduled clinic appointment visits. Weekly short text messages will also be sent to clients to remind them of taking their medications. The control group will only receive standard care and paper-based appointment during clinic visits. Both groups of clients will be followed up for a period of 6 months on ART. Repeated CD4 count, viral load, Weight, TB status and OI index assessment and measurements will be conducted at 3 and 6 months, respectively to determine treatment outcome. Medication adherence will be measured using structured self-report questionnaires. Clinic visits will be measured through medical records of clinic attendance and clinicians' notes.

**Study Duration:** Recruitment and data collection will be from December 2013 to February 2015.

**Study population:** The study population is all HIV positive clients assessed and found to be eligible for ART commencement at Hospital Sungai Buloh, Selangor

**Inclusion criteria:** Age range of 15 to 65 years eligible to commence ART, able to read text messages and have a mobile phone access.

**Exclusion criteria:** Clients who are previously or currently on ART, foreigners & pregnant patients

**Sampling frame:** It is the list of all HIV positive clients assessed and found to be eligible for ART from December 2013 to August 2014 in Hospital Sungai Buloh, Selangor

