| Clinical (Wt, TB & OI status)                   | Clinician's notes       | Clinicians/nurses/adherence counsellors          | Every visit                                       |
| Immunological (CD4)
Virological (viral load) | Laboratory records      | Laboratory scientists                            | Baseline & 6mths                                  |
| Medication adherence                            | Adherence questionnaire | Research assistants/nurses/adherence counsellors | Baseline, then every visit (particularly 3&6mths) |

- **Data Storage:** All data generated from this study will be stored for a maximum of 3 years after the completion of the study, after which they will be destroyed. However, during this period they will remain joint intellectual property of Universiti Putra Malaysia and Hospital Sungai Buloh.

**Primary Outcomes:** The first primary outcome is (improved) patient adherence to ART at six months. This is assessed by self-report using a standardized questionnaire of the number of pills missed in the last 30 days and calculating percent adherence based on the expected number of doses taken and/or number of missed doses. Percent adherence will be analyzed as continuous variable and polytomous variable. Subjects will be considered as "Good adherence" when they achieve an optimal adherence cut of >95% of medications taken as directed with <3 missed doses in the last 30 days period. "Fair adherence" will be considered as 80-95% of medications taken as directed with 3-8 missed doses in the last 30 days period, while "Poor adherence" will be considered as <80% of medications taken as directed with >8 missed doses in the last 30 days period. Medication adherence will be assessed at each follow-up visit, particularly at months 3 and 6. The six month scheduled follow-up is the primary analysis but the three month assessment will allow for evaluating trends but is not the primary outcome.

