The other secondary outcome is (improved) immunologic status/response of patients at six months. This will be assessed based on records of two (2) laboratory measurements – CD4 T cell count and viral load. Patients' CD4 count results at six months will be assessed and compared with baseline values to determine if there's a consistent increase (or otherwise) as expected with strict medication adherence. If patients are adherent to ART regimens, absorb the drugs normally, and if their virus is not resistant to the ART drugs in the regimen, it is expected that their CD4 count should increase from baseline levels by at least 50 cells per microliter of blood within 6-12 months of initiating treatment. CD4 count value at six month scheduled follow-up is the primary analysis.

Similarly, plasma HIV RNA load results at six months will be assessed and compared with baseline levels to determine if there is a significant suppression at six months. If patients are adherent to ART regimens, absorb the drugs normally, and if their virus is not resistant to the ART drugs in the regimen, it is expected that their plasma HIV load should be suppressed to undetectable levels (<400 copies/ml) by six months and remain suppressed thereafter. Analysis of "suppressed" (<400 copies/ml) versus "failure to suppress" (>400 copies/ml) at six months as a dichotomous variable is the primary analysis.

**Data analysis:** Data collected will be collated, checked, cleaned, entered into and analyzed using Statistical Package for Social Sciences software (SPSS) version 21 and AMOS software. Parametric tests (T-test, repeated measures ANOVA) and non-parametric tests will be conducted on the data. P value for test of significance of results will be set at 0.05, alpha level (Type 1 error) at 0.05 (Confidence Interval of 95%), Power at 80% to detect an impact of 15% in the fraction of patients with adherence of at least 90% (assuming a no intervention median adherence level of 90%) using a two-tailed test, Z=1.96, and strength by effect size analysis. Analysis will be by intention-to-treat and complete case analysis.

| Independent variable                                                    | Dependent variable                                                           | Type of analysis                                                           |

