|-------------------------------------------------------------------------|------------------------------------------------------------------------------|----------------------------------------------------------------------------|
| Categorical (socio-demographic, behavioural & adherence factors) | Continuous (Wt, CD4, viral load)                                      | T-test, Repeated Measures ANOVA                                     |
| Categorical & Continuous (All IVs)                           | Categorical (adherence level, TB status, OI index, viral suppression) | Multivariate/Multinomial Logistic Regression Model                  |
| Categorical (All IVs converted to categorical)                   | Categorical (All DVs converted to categorical)                        | -Structural Equation Modelling
-Chi-square (sub-group analysis) |

**Limitations:** (1) Self-report of adherence – exaggeration of true adherence (Pharmacy refill records, CD4 count and viral load will provide a means of validating the responses)

(2) Pill count will not be used

(3) Structured questionnaires may not elicit in-depth information

**Ethical considerations:** The study and materials will be presented to the UPM Ethics approval committee and the Malaysian Ministry of Health's Institutional Review and Ethics Committee for review and approval. Thereafter, permission will be sought from the Medical Director of the hospital in writing to use their clients. The researcher will work in collaboration with attending clinicians, nurses and pharmacists in identification and monitoring of the clients.

**Expected outcomes:** The expected outcomes of this research include:

1. A significant difference in treatment adherence (medication adherence and regular, scheduled clinic attendance) is expected in the intervention group compared to the control group.
2. Better clinical outcome in the intervention group compared to the control group.
3. Socio-demographic, psychosocial and other risk factors that determine differences in treatment adherence between the intervention and control groups will be identified.
4. Provide baseline information on the effectiveness of current standard of care (routine adherence counselling) on treatment adherence and clinical outcomes.

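### The analysis table does not separate the randomised comparison (H2) from the adherence–outcome association (H3), and it compares CD4 and weight without baseline adjustment

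*Protocol*

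**What the plan says.** All places are in the Protocol, section B (Research methodology), unless stated.

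- **Analysis table, first row.** Independent variables are "socio-demographic, behavioural & adherence factors"; dependent variables are "Wt, CD4, viral load"; methods are "T-test, Repeated Measures ANOVA".
- **Second row.** All independent variables, categorical and continuous, enter multivariate or multinomial logistic models for "adherence level, TB status, OI index, viral suppression".
- **Third row.** All variables are categorised ("All DVs converted to categorical") for structural equation modelling and a chi-square test labelled as sub-group analysis.
- **Not named in any row.** The study arm, and scheduled clinic attendance, which Primary Outcomes makes the second primary outcome.
- **Hypotheses (Introduction).** H2 is the comparison of reminders with routine counselling. H3 and Objective 4 concern the relation of adherence to outcome.
- **Secondary Outcomes.** Month-6 CD4 and clinical status are compared with baseline, and "CD4 count value at six month scheduled follow-up is the primary analysis".
- **Laboratory schedule.** Study Design includes CD4 and viral load in a list ending "OI index assessment and measurements will be conducted at 3 and 6 months", and Data collection (Who and When) also gives baseline, month 3 and month 6. The data-source table gives "Baseline & 6mths" for both tests.

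**The concern.** H2 is the trial's causal question, and the table has no row that plainly answers it. The second row is the nearest candidate, and it leaves two readings. If arm is not among the independent variables, the row does not test H2. If arm is among them, it shares the model with the adherence factors. On-treatment adherence is measured after randomisation, is itself the first primary outcome, and is how reminders are expected to improve viral suppression, TB and OI status. Holding it fixed removes part or all of the effect H2 asks about. An analyst following the table could then report no arm effect on suppression when there was one.

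The second issue is efficiency. Baseline CD4 and weight are collected, but no model uses them as covariates. The arm comparison stays valid, but its intervals may be wider than the data allow. The conflict over month-3 tests adds to this, because it decides which time points a repeated-measures analysis of CD4 or viral load can contain.

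**Working it through.** **1. The plan's own figure.** Inputs from Sample size: SD 132, difference 550 − 500 = 50, z-values 1.96 and 0.842 (sum 2.802).

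n per group = 2 × 132² × 2.802² / 50² = 109.4, rounded up to 110; 110 × 1.10 = 121. The stated figures reproduce. The printed formula omits the square on the difference (taken literally it gives about 5,472), but this is a slip in the notation and the 110 stands.

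**2. Detectable CD4 difference with 80% power at 110 per group.** I take 132 as the SD of a single CD4 value, equal at baseline and month 6. The correlation r between the two is not in the protocol, so a range is assumed.

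- Unadjusted month-6 comparison: 2.802 × 132 × √(2/110) = 49.9 cells.
- Change score: 49.9 × √(2(1 − r)). This is the group-by-time test of a repeated-measures ANOVA with two time points.
- ANCOVA on baseline: 49.9 × √(1 − r²).

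| r (assumed) | Unadjusted | Change score | ANCOVA |
|---|---|---|---|
| 0.3 | 49.9 | 59.0 | 47.6 |
| 0.5 | 49.9 | 49.9 | 43.2 |
| 0.7 | 49.9 | 38.6 | 35.6 |
| 0.8 | 49.9 | 31.5 | 29.9 |

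Against the unadjusted comparison, ANCOVA gains 6.7, 14.3 and 20.0 cells at r = 0.5, 0.7 and 0.8. Against the change score it gains 6.7, 3.0 and 1.6 cells. In power for 50 cells, the unadjusted comparison has 80.2%. At r = 0.3, 0.5, 0.7 and 0.8 the change score has 66.1%, 80.2%, 95.2% and 99.3%, and ANCOVA has 83.8%, 90.0%, 97.6% and 99.7%. ANCOVA is the most precise of the three throughout this range; the change score is worse than no adjustment when r is below 0.5.

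**3. Conditioning on adherence: an illustration with assumed rates.** Suppose Good adherence is 50% in control and 65% with reminders, suppression is 90% with Good adherence and 60% without, and the arm acts only through adherence.

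- Reminders: 0.65 × 0.90 + 0.35 × 0.60 = 79.5%.
- Control: 0.50 × 0.90 + 0.50 × 0.60 = 75.0%.
- Total arm effect: 4.5 points. Within each adherence level: 0.

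With suppression without Good adherence at 70% or 50% instead of 60%, the total effect is 0.15 × 0.20 = 3.0 or 0.15 × 0.40 = 6.0 points, again 0 within levels. If part of the effect bypasses adherence, only the part through adherence is lost.

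**4. Is the adherence in the table on-treatment?** Patients are ARV-naïve (Sampling unit), so adherence to ART can only be observed after treatment starts. The baseline questionnaire does collect adherence-related items such as readiness, social support and reasons for missing medication. The table's term covers both kinds and does not distinguish them.

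**The case against.** The strongest reply is that the table serves every objective, not only H2. Adherence as a predictor of outcome is what Objective 4 and H3 require, and predicting adherence level from readiness, support or alcohol use fits Objective 1. The intention-to-treat statement and the expected outcomes show that arm comparisons are planned. The exact model and covariates per endpoint can sit in an SAP that is not shown.

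Much of this stands. Leaving arm and attendance unnamed would on its own be missing detail. What remains is that the printed table specifies one set of predictors for outcomes that serve both H2 and H3, and specifies unadjusted methods for CD4 and weight.

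Three stronger readings are tempting, and the document does not support them.

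- *Baseline is ignored.* It is not. Secondary Outcomes compares clinical status and CD4 with baseline, and repeated-measures ANOVA can include baseline as a time point. Only covariate adjustment is absent. Its absence costs precision and does not bias the randomised comparison.
- *The adherence model is circular.* The term may partly mean baseline items, so circularity is not shown.
- *H2 cannot be estimated, or its effect is driven to zero.* A model without arm attenuates nothing, and the fall to zero above depends on assumed full mediation.

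Quoting the ANCOVA gain only against the month-6 t-test would also overstate it, since the plan names repeated-measures ANOVA too.

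**Conclusion.** The concern holds in a limited form. The table mixes the randomised comparison with the adherence–outcome association. If arm is one of the independent variables, the models for viral suppression, TB and OI would condition on on-treatment adherence and could understate the reminder effect. The size depends on how much of the effect runs through adherence. The protocol does not give this, and the illustrative 3.0 to 6.0 points is the full-mediation case.

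The planned CD4 and weight comparisons are valid but less precise than they could be. For CD4, ANCOVA lowers the detectable difference by 6.7 to 20.0 cells against the unadjusted month-6 comparison for r from 0.5 to 0.8. Against a two-time-point change score the gain is 1.6 to 6.7 cells, smallest at high r. These figures assume SD 132 at both times, 110 patients analysed per group, and the stated values of r. The SD of weight is not given, so no gain is quantified there.

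The conflict over the month-3 laboratory tests is plain on the page.

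**What to change.** 1. Add rows for H2. Regress Good adherence, Regular attendance and viral suppression on arm plus baseline (pre-ART) covariates only. Apply the same restriction to any arm comparison of TB and OI status. The covariates should be described as pre-ART because Study Design places the baseline assessment after allocation.
2. Analyse month-6 CD4 and weight by ANCOVA on arm and the baseline value.
3. Keep on-treatment adherence as a predictor only in separate models, labelled observational, for Objective 4 and H3. State which adherence factors are baseline items and which are measured on treatment.
4. Reconcile the CD4 and viral load time points between Study Design, Data collection (Who and When) and the data-source table, and state which time points any repeated-measures analysis uses.

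The cost is rewriting a three-row table and reconciling one schedule entry. The outcomes and baseline values needed for items 1 to 3 are already to be collected, and the sample size need not change.

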#### **Objectives of study:**

The general objective of this study is:

- To determine the effectiveness of mobile phone technology (SMS and Phone call reminders) in improving clinic attendance, medication adherence and outcome of treatment among HIV patients on ART.

The Specific objectives include:

1. To determine socio-demographic factors that affect treatment adherence and contribute to treatment default and Lost-to-follow-up (LTFU) among HIV patients on ART.
2. To develop and implement a 'reminder module' (delivered via SMS and telephone calls) to improve clinic attendance and medication adherence among HIV patients on ART.
3. To determine the effectiveness of SMS and telephone call reminders in improving clinic attendance and medication adherence among HIV patients on ART.
4. To determine the effect of medication adherence on the clinical and immunological outcome of HIV patients on ART.

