### Research hypotheses:

**H1:** There is no significant difference in the socio-demographic characteristics of HIV patients who adhere very well to their ART compared to those who do not.

**H2:** The application of mobile phone technology (SMS and phone call reminders) will significantly improve treatment adherence and clinical outcomes of HIV patients on ART, when compared to routine adherence counselling and paper-based appointment scheduling alone.

**H3:** There is a strong and direct relationship between Good adherence to treatment (regular clinic visits and strict medication adherence) and outcome of antiretroviral treatment among HIV patients on ART.

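### Objective 4 claims an effect of adherence, but the tests named for continuous CD4, weight and viral load adjust for no confounder

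*Protocol*

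**What the plan says.** All references are to the protocol.

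- **Objectives of study, Objective 4:** "To determine the effect of medication adherence on the clinical and immunological outcome of HIV patients on ART". This is causal wording.
- **Research hypotheses, H3:** "There is a strong and direct relationship between Good adherence to treatment (regular clinic visits and strict medication adherence) and outcome of antiretroviral treatment". This claims a relationship and names neither CD4 nor weight.
- **Research methodology, Data analysis table, row 1:** the independent variables are categorical ("socio-demographic, behavioural & adherence factors"), the dependent variables are continuous ("Wt, CD4, viral load"), and the analysis is "T-test, Repeated Measures ANOVA". No covariate is named.
- **Row 2:** "Multivariate/Multinomial Logistic Regression Model" with all independent variables, for adherence level, TB status, OI index and viral suppression.
- **Row 3:** "Structural Equation Modelling" and chi-square, with every independent and dependent variable first made categorical.
- **Primary Outcomes:** adherence is self-reported over 30 days and graded Good, Fair or Poor during follow-up.
- **Secondary Outcomes:** six-month CD4 and weight are to be compared with baseline, yet the six-month CD4 value is also called the primary analysis for CD4.

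**The concern.** Patients choose, or fall into, their adherence level. Objective 1 sets out to find socio-demographic factors that affect adherence. The literature review lists depression, drug and alcohol abuse, and co-morbidities among the factors linked to poor adherence, and low income and education in some studies. Several of these can also affect CD4, weight and viral load directly. Study arm is a further candidate: the intervention is meant to change adherence, and it also brings extra counselling that could act on outcome by other routes.

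For the continuous outcomes, a bare comparison of adherence groups therefore mixes any effect of adherence with the effect of being the kind of patient who adheres. Because Objective 4 speaks of an effect, the trial could report that mixture as causal. The protocol names these tests itself, so this is not merely detail left for an analysis plan.

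**Working it through.** **1. The plan's own figure.** The sample size section uses SD 132 and a difference of 50 cells. With the difference squared, n = 2 × 132² × (1.96 + 0.842)² / 50² = 109.4, so 110 per arm; with 10% added this is 121 per arm and 242 in all. The point here does not dispute that figure. It supplies the SD and a yardstick of 50 cells.

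**2. Where adjustment exists.**

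| Outcome | Named analysis | Adjusted for other factors? |
|---|---|---|
| Weight, CD4, viral load, continuous | t-test, repeated-measures ANOVA | No covariate named |
| Viral suppression, TB status, OI index | Logistic regression, all independent variables | Yes |
| All outcomes, categorised | Structural equation model, chi-square | Model is multivariable; no paths or confounders named |

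**3. Illustration A: good adherers start with higher CD4 and adherence has no true effect.** From the protocol: SD 132, two-sided 5%. Assumed: 218 patients (242 × 0.9), 70% good adherers (153 v 65), baseline-to-month-6 correlation 0.7, two time points, and a baseline gap of 20, 40 or 60 cells. Rejection = P(Z > 1.96 − b/SE) + P(Z < −1.96 − b/SE), where b is the spurious difference.

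- √(1/153 + 1/65) = 0.148.
- Month-6 value: SE = 132 × 0.148 = 19.5.
- Change, which is group-by-time with two time points: SE = 132 × √(2 × 0.3) × 0.148 = 15.1.
- Month 6 adjusted for baseline: SE ≈ 132 × √(1 − 0.49) × 0.148 = 14.0.

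| Analysis | Gap shrinks to 0.7 of its size: b, rejection | Gap persists: b, rejection |
|---|---|---|
| t-test, month 6 | 14/28/42 cells; 11/30/57% | 20/40/60 cells; 18/53/87% |
| Group-by-time | −6/−12/−18 cells; 7/12/22% | 0 cells; 5% |
| Adjusted for baseline CD4 only | 0 cells; 5% | 6/12/18 cells; 7/14/25% |

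Simulations of 3,000 to 4,000 runs per setting agree to within a few points. For the t-test they gave 11%, 29–31% and 57–58% when the gap shrinks. For baseline adjustment they gave 7–8%, 13% and 23–24% when it persists. The ANOVA group main effect rejected in 16% to 92% of runs across these settings.

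**4. Illustration B: no baseline CD4 gap, but a covariate drives both adherence and CD4 gain.** Assumed: 220 patients (154 v 66), correlation 0.7 as before, a covariate 0.5 SD higher in good adherers, and 30 cells of gain per SD. The spurious difference is 0.5 × 30 = 15 cells. In 2,000 simulated trials the month-6 t-test rejected in 13%, group-by-time in 16%, and change adjusted for the covariate in 5%.

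**The case against.** The strongest reply has four parts.

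- **Baseline is used.** Repeated-measures ANOVA is named, and the Secondary Outcomes text compares six-month results with baseline. This stands in part. A reader might infer that the ANOVA necessarily reports baseline differences as an effect, but the group-by-time term holds 5% under a persistent gap. The protocol does not say which term is tested, and Illustration B shows that group-by-time is still confounded.
- **Row 1 is not the only analysis.** A reader might infer that Objective 4 rests wholly on unadjusted tests. It does not: row 2 adjusts viral suppression, TB and OI status, and row 3 brings CD4 and weight into a multivariable model. Row 3 does so only after categorisation, so it gives no adjusted estimate for these outcomes on their measured scale.
- **The test and hypothesis are read too harshly.** A reader might infer that a t-test is assigned to the three adherence levels, or that H3 is causal. The table covers many factors and lists ANOVA beside the t-test, and H3 speaks of a relationship. Neither inference is supported.
- **The numbers are assumed, and covariate lists often sit in an analysis plan.** The first half is right: the protocol gives no baseline gap, share of good adherers or correlation, and does not say whether a gap would persist. Nor is adjusting for baseline CD4 alone a complete cure, since it too rejects too often when the gap persists. The second half carries less weight, because the protocol does name methods for these outcomes and they do not support its stated objective.

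**Conclusion.** The point holds in a limited form. For continuous CD4, weight and viral load, the named tests compare self-selected adherence groups without confounder adjustment, while Objective 4 calls the result an effect. A month-6 t-test or an ANOVA group main effect carries baseline differences through. The group-by-time term removes a stable gap but not confounding of the change.

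The size is unknown. Under the stated assumptions the month-6 t-test gives false positives in about 11% to 58% of trials for a shrinking gap of 20 to 60 cells, with spurious differences of 14 to 42 cells against the protocol's 50-cell yardstick. Other assumptions give other figures, and the ranking of baseline adjustment against group-by-time reverses with them. The conclusion rests on the non-randomised exposure and the missing adjustment, not on any one percentage.

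This concerns a non-randomised objective on secondary outcomes. Neither the randomised comparison nor the two primary outcomes is affected.

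**What to change.** - For month-6 CD4, weight and log10 viral load, name a linear model on adherence (percent, or the three levels) adjusted for the baseline value of the outcome, study arm, age, gender, baseline WHO stage and alcohol/drug use.
- Report the change-from-baseline (group-by-time) analysis as a sensitivity analysis, since each approach handles a different pattern of baseline gap.
- Reword Objective 4 as an association. H3 already speaks of a relationship, so it needs little more than consistency with that wording.
- Present the randomised arm comparison separately from the adherence analysis.

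The cost is a change of wording and a little more analysis. The covariates are already to be collected through hospital records, WHO staging at clinic visits and section G of the baseline questionnaire. The claim becomes more modest, and residual confounding by unmeasured factors remains.
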